### Duration of Study

The optimum length of the study will be 12 weeks, if feasible, and if not, at least 2 weeks would be necessary.

### Assignment of Interventions

For treatment allocation, randomization (1:1:1:1) and blinding protocol will be used as described previously [71].

### Proposed Outcome Measures

#### Primary Outcome Measures to Be Assessed

*Subset A* denotes the change in BMI, total body fat, body weight, percentage body fat, lean body mass, percentage lean body mass, waist circumference, and waist-hip ratio from baseline to 12 weeks (time frame: 0, 6, 12, and n weeks). The measurements will be performed with light clothing before breakfast and preferably after voiding.

*Subset B* denotes changes in HSP-27, HSP-65, HSP-70, HSP-72, and HSP-90 (in plasma and total leukocytes) and anti–HSP-27, anti-HSP-65, anti-HSP-70, anti-HSP-72, and anti-HSP-90 antibodies from baseline to 12 weeks (or whatever time is feasible, time frame: 0, 6, 12, and n weeks).

*Subset C* denotes changes in motilin, fasting glucose, insulin, C-peptide, 2-hour glucose, and insulin plus homeostasis model assessment–estimated insulin resistance from baseline to 12 weeks (or whatever time is feasible, time frame: 0, 6, 12, and n weeks).

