### Sample Size Calculation

As the choice of type I errors (α, false positive), type II errors (β, false negative), and effect size may be quite arbitrary [79], we suggest calculating the sample size or power using the *R* value (eHSP-70 to iHSP-70 ratio) for a pilot study (alternatively, owing to feasibility, a preliminary study may be conducted on mice or rats).

Furthermore, as providing a priori sample size calculation is misleading and the presentation of CIs—although serving the same purpose—is superior [80], it would be better to use the CI of the *R* value to calculate the sample size based on the feasibility of a priori assumptions about the study results and available resources. In addition, because foods and drinks may be served and consumed at even wider temperature ranges, it would be instrumental to calculate sample sizes based on wider *R* ranges (approximately 0.2-6).

According to Krause et al [30], assuming the ratio *R* = (eHSP-70) / (iHSP-70) = 1 for the controls (resting and unstimulated) and assuming a moderate-hot meal temperature may produce a shift in *R* to up to 5, which is paralleled by an increase in inflammatory markers and stimulation of cell proliferation, *R* values >5 can be considered as an exacerbated proinflammatory response. However, for a conservative calculation, we suggest using *R=*2*.* According to Hunter-Lavin et al [81], heat-shocked cells simultaneously measured HSP-70 at 37 °C (*R*=1.00), 39 °C (*R*=1.45), 42 °C (*R*=0.65), 43 °C (*R*=0.48), and 45 °C (*R*=1.97), this later temperature confirms a proinflammatory response.

Note that at 45 °C (*R*=1.97), there is a turning point compared with that at 43 °C. This means that if a study intends to investigate wider ranges of meal temperature, it is necessary to calculate an array of expected *R* values and then choose the maximum calculated sample size. For an *R* value between 0.22 and 1.1, a sample size of 9 participants is needed to achieve 80% power [1], whereas an *R* value between 1.8 and 6 would require 75 participants to achieve 90% power [2].

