Changes in the calculation of the *R* value are suggested to be valid during heat exposure, as *R* values are associated with the heat exposure of peripheral blood mononuclear cells to different temperatures within a physiological range [30]. Precautions that should be considered could include, but are not limited to, correction for noncompliance of the participants, adjustment for multiple comparisons, and innovative study design.

A total of 80 patients will be randomized equally (1:1:1:1) between the 3 active treatments and the thermoneutral group. Overall, 20 participants will be randomly allocated to the thermoneutral diet group (37 °C): 20 at 42 °C, 20 at 49 °C, and 20 at 54 °C. The primary analysis will be intention-to-treat for the whole study cohort.

It is possible that there are multiple roles of HSPs in body weight, weight regain, and composition, probably related to the exposure time during diet ingestion (and also dietary temperature acclimatization during short-term periods, midterm periods, and long-term periods and presence or absence as well as the degree of insulin resistance in people). Thus, conducting a clinical trial for 12 weeks would provide a sufficient time course to investigate this point.

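### The protocol names 29 to 30 co-equal primary outcomes without a hierarchy or a fixed time point; separately, its sample size rests on a ratio that is not a listed outcome

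*Protocol article*

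**What the plan says.** The section Primary Outcome Measures to Be Assessed gives three subsets, with no order among or within them:

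- Subset A: "the change in BMI, total body fat, body weight, percentage body fat, lean body mass, percentage lean body mass, waist circumference, and waist-hip ratio".
- Subset B: "changes in HSP-27, HSP-65, HSP-70, HSP-72, and HSP-90 (in plasma and total leukocytes", and antibodies to the same five proteins, ending "anti-HSP-65, anti-HSP-70, anti-HSP-72, and anti-HSP-90 antibodies from baseline to 12 weeks".
- Subset C: "changes in motilin, fasting glucose, insulin, C-peptide, 2-hour glucose, and insulin plus homeostasis model assessment–estimated insulin resistance".

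Subsets B and C are timed "from baseline to 12 weeks (or whatever time is feasible, time frame: 0, 6, 12, and n weeks". Subset A has the same open week n but not the feasibility clause. Duration of Study adds: "The optimum length of the study will be 12 weeks, if feasible, and if not, at least 2 weeks would be necessary". Against this, Measures has every outcome taken at 0, 6 and 12 weeks, and Sample Size Calculation argues that 12 weeks is long enough to answer the question.

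On sizing, "we suggest calculating the sample size or power using the" is followed by R, the ratio of extracellular to intracellular HSP-70. The section quotes 9 participants for 80% power (R from 0.22 to 1.1) and 75 for 90% power (R from 1.8 to 6). It sets 80 participants, 20 per arm, in three active arms and a 37 °C arm. Among precautions that should be considered it gives "adjustment for multiple comparisons" as an example.

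**The concern.** A primary outcome is the result by which the trial is judged, fixed before the data are seen. Here the variable, the time point and the contrast are all open, so whichever combination looks best could later be reported as primary. With this many candidates, at least one nominally significant result is likely by chance unless the error rate is controlled.

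Two features make the choice matter more. Statistical Analyses plans, where feasible, an adaptive design favouring arms that perform better at interim looks, and with some 30 co-equal primaries that ranking has no definition. Also, the cell-culture R values quoted for 37, 39, 42, 43 and 45 °C (1.00, 1.45, 0.65, 0.48, 1.97) rise, fall and rise again, so a change in either direction could be read as support.

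The sizing problem is distinct. If R is not an outcome, a sample size derived for R says nothing about the power or precision for weight, insulin or any other listed primary.

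**Working it through.** **1. Count of primary outcomes.** Subset A has 8. Subset B has 5 proteins × 2 compartments + 5 antibodies = 15. Subset C has 6, or 7 if insulin after the glucose load is a second insulin measure. Total: 8 + 15 + 6 = 29, or 30. Without separate counting of plasma and leukocytes, subset B has 10 and the total is 24 or 25.

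**2. The plan's own sample-size figures.** These cannot be reproduced, because no SD, alpha or test is given. Taking the width of each R range as the difference, two-sided 5% and n per arm, the implied SD is Δ / √(2(z_α + z_β)²/n):

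- n = 9: Δ = 1.1 − 0.22 = 0.88; SD = 0.88 / √(2 × (1.960 + 0.842)²/9) = 0.67.
- n = 75: Δ = 6 − 1.8 = 4.2; SD = 4.2 / √(2 × (1.960 + 1.282)²/75) = 7.9.

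Read as total numbers, they imply 0.47 and 5.6. Under any of these readings the figures concern R and no listed outcome.

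**3. Chance of at least one false-positive primary result.** Alpha is not stated; two-sided 0.05 per test, unadjusted, is assumed. For k independent tests the chance is 1 − 0.95^k:

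- k = 24 or 25: 70.8% or 72.3%
- k = 29 or 30: 77.4% or 78.5%
- k = 3 × 30 = 90: 99.0%

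The expected number of false positives is 30 × 0.05 = 1.5, or 90 × 0.05 = 4.5.

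The outcomes are correlated, and comparisons sharing one control arm are not independent. A null simulation therefore used 4,000 trials, four arms of 20, and normal outcomes with a common correlation. Its Monte Carlo standard error is at most √(0.5 × 0.5/4000) = 0.8 percentage points. The correlations are assumptions; the protocol gives none. Results for 29 and 30 outcomes:

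| Correlation | One omnibus test per outcome | Three comparisons with 37 °C per outcome |
|---|---|---|
| 0 | 78% | 97–98% |
| 0.3 | 66–67% | 93–94% |
| 0.5 | 54% | 84–85% |
| 0.8 | 27–28% | 53% |

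Letting correlation differ by subset (A 0.8, B 0.3, C 0.5) gives 65% and 93%. Higher values (A 0.9, B 0.5, C 0.6) give 56% and 87%. All of these are for one time point.

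**4. Cost of keeping all outcomes primary.** Bonferroni would need 0.05/30 = 0.0017 per outcome or 0.05/90 = 0.00056 per comparison. With 20 per arm, the difference detectable with 80% power is (z_α + z_β) × √(2/20): 0.89 SD at 0.05, 1.26 SD at 0.0017 and 1.36 SD at 0.00056.

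**5. Time points side by side.** A 2-week study, allowed under Duration of Study, cannot supply the 6- and 12-week values that Measures requires, or the 12-week change that all three primary subsets name. These passages must be reconciled.

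**The case against.** A reader might infer that a positive primary result is all but guaranteed by chance. The document does not support that. Near certainty requires some 90 unadjusted, weakly correlated tests at 5%. The protocol states no alpha, does not say that tests will be unadjusted, does not specify pairwise tests against 37 °C, and says that multiplicity precautions should be considered. Several outcomes, such as BMI and body weight, are close to duplicates, which lowers the figure. This part of the objection stands, and the size must be given as a conditional range.

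It is also fair that R's absence from the outcome lists does not itself raise the false-positive risk, and that both HSP-70 measures from which R could be formed are already in subset B. The feasibility clause is not in subset A. Each subset does name the change from baseline to 12 weeks.

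Two further arguments carry less weight. One is that the multiplicity method belongs in an analysis plan. That is true of the method, but the list of primary outcomes and their timing is stated here, and a later plan would have to override it. The other is that this is a hypothetical pilot, not yet started. It nevertheless specifies 80 randomized participants and an intention-to-treat primary analysis, which names a population but no variable; and not having started makes correction cheap.

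**Conclusion.** The point holds in a limited form. The protocol fixes its primary result badly: 29 to 30 unranked outcomes (24 to 25 on the narrower count), an open week n in all three subsets, a feasibility clause in two, and a possible 2-week study that conflicts with its own measurement schedule and 12-week rationale.

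If each outcome is tested once at an assumed unadjusted 5%, the chance of at least one false-positive primary result is about 78% under independence and about 27% at correlation 0.8. With three comparisons per outcome it is about 97–98% and 53%. Even the lowest figure is more than five times 5%, before any choice among time points.

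The mismatch between R and the outcome lists is a second, independent defect: the figures 9 and 75 support no listed primary outcome.

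**What to change.** Name one primary outcome at week 12, analysed with its baseline value as covariate, each active arm compared with 37 °C under Dunnett adjustment. Move the remaining items of subsets A to C to secondary or exploratory. Delete week n from all three subsets and the feasibility clause from B and C, and align the secondary and other lists. Reconcile Duration of Study with Measures, and state that a shortened study is a feasibility study that draws no 12-week conclusion.

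Which variable to choose is a scientific judgement, but sizing must follow it:

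- If R is primary, define it from the listed plasma and leukocyte HSP-70, and give the SD, alpha and test behind the sample size. Also reconcile the sampling: Measures draws blood after a 12-hour fast, whereas Sample Size Calculation treats changes in R as valid during heat exposure.
- If body weight is primary, state that the R-based calculation does not support it and give the precision that 20 per arm provides. Before Dunnett adjustment, dropout or any gain from the baseline covariate, the 95% confidence interval for a difference between two arms has a half-width of about 1.96 × √(2/20) = 0.62 SD.

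The cost is protocol wording and one recalculation. The downside is that most listed outcomes lose primary status.

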#### Secondary Outcome Measures to Be Assessed

Changes in total cholesterol, triglycerides, low-density lipoprotein, high-density lipoprotein, reactive oxygen species, reactive nitrogen species, and NF-κB from baseline to 12 weeks (or whatever time is feasible, time frame: 0, 6, 12, and n weeks) are to be assessed.

#### Other Outcome Measures to Be Assessed

*Subset A* denotes plasma levels of leptin and adiponectin from baseline to 12 weeks (or whatever time is feasible, time frame: 0, 6, 12, and n weeks).

*Subset B* denotes possible changes in appetite and food intake (using a 3-day dietary recall questionnaire). Immediately before and after each diet, participants will rate hunger, satiety, and prospective food consumption using 100-mm visual analog scales. Gastric motility will be measured using ultrasound imaging systems.

### A Short Proposal to Conduct a Crossover Design

As there are between-individual responses to heat stress [72], there are also interindividual differences in the serum concentration of HSPs [73-75], which may confound statistical analyses when calculating interactions between frequency of drinking or eating hot foods and time elapsed after eating or drinking. To overcome issues with interindividual differences in its broad sense, a crossover design with necessary modifications can be performed. In this case, it will be necessary that participants can eat ad libitum.

A 2-week washout period and thermoneutral diet between conditions will be included, in which participants will eat boluses of soups served at approximately 37 °C. In this case, the order in which participants participate in each treatment will be randomized. The participants will be assigned 4 weeks of each treatment with a 2-week washout period between each of the 4 crossover treatments.

Before starting the second round of the trial, all 3 treatment groups will return to a thermoneutral bolus diet for another 5 weeks (5 weeks of active treatment, 2 weeks of washout period, and 5 weeks of crossover round).

Adipose tissue biopsies and plasma samples will be obtained at 2 time points: before and after dietary treatment diet.

### Statistical Analyses

For statistical analysis, Bayesian adaptive approaches [76] will be applied whenever feasible because this approach is more likely to allocate participants to better-performing arms at each interim analysis.

In addition to standard analyses of RCTs, causal mediation analysis can be performed to determine how much of the weight change is mediated by the increase in HSP levels or appetite or both. Future trials should seek to identify alternative mechanisms with the aim of further refining the intervention.

This seminal clinical trial can provide preliminary data for causal mediation analysis to facilitate the exploration of the causal mechanisms underlying possible energy contributions through higher dietary temperatures. Proper methods will be used for this purpose [77,78].

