### A Proposal to Conduct an RCT

A 4-arm randomized design investigating diets served at different temperatures in 5 °C increments (with core body temperature as a reference) in healthy adults would be the first step to elucidate the potential mechanism linking higher meal temperature with energy contribution. The same protocol can be replicated in patients who are overweight and obese or in people with T2DM. In addition, a crossover design can be performed with necessary modifications.

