### Participants: Inclusion and Exclusion Criteria

The participants will include 80 healthy (BMI 25-35 kg/m^2^) men and women aged 19-65 years. Entry criteria will include people who are not currently dieting to lose weight and have had no weight loss or gain >2 kg over the past 3 months; not taking any medications (including antifever) that affect energy expenditure or eating; not using tobacco; not pregnant or lactating or planning to become pregnant in the next 12 months; and have no limitations to eating specific foods or to swallowing (eat and drink) a normally estimated range of meal temperatures (37-52 °C). The participants must not have major health problems; known cardiovascular (cardiac, peripheral vascular, and cerebrovascular), pulmonary (chronic obstructive pulmonary disease, interstitial lung disease, and cystic fibrosis), or metabolic (diabetes, thyroid disorders, and renal or liver disease) disease; and severe fever.

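### The conditional plan for interim-driven allocation is not reconciled with the unconditional 1:1:1:1 randomisation of 20 per arm, and a better-performing arm is not defined

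*Protocol article*

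**What the plan says.** Three sections of the protocol article bear on how participants reach their arms.

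- **Statistical Analyses:** Bayesian adaptive methods are to be used where feasible, the stated ground being that "this approach is more likely to allocate participants to better-performing arms at each interim analysis". The reason given concerns allocation, not only Bayesian inference.
- **Assignment of Interventions:** "For treatment allocation, randomization (1:1:1:1) and blinding protocol will be used as described previously".
- **Sample Size Calculation:** "A total of 80 patients will be randomized equally (1:1:1:1) between the 3 active treatments and the thermoneutral group". The arm sizes follow: "20 participants will be randomly allocated to the thermoneutral diet group (37 °C): 20 at 42 °C, 20 at 49 °C, and 20 at 54", with all temperatures in °C. Intention-to-treat is named as the primary analysis.

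Two other places matter. A Proposal to Conduct an RCT says that the four-arm comparison "would be the first step to elucidate the potential mechanism linking higher meal temperature with energy contribution". The primary outcome section lists three subsets (body size and composition; HSPs and anti-HSP antibodies; motilin, glucose and insulin measures), names none as leading, and gives no direction that counts as benefit.

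**The concern.** A ratio that follows interim results is not a fixed 1:1:1:1 ratio, and arms fed by such a rule will not in general finish at 20 each. A team building the randomisation system from this article cannot tell which scheme to build.

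The adaptive rationale also has no stated target. Adaptation needs an outcome and a direction, and the article supplies neither. The hypothesis is that hotter food raises HSPs and contributes to obesity. If better performance meant less weight gain, a working rule would thin out the hot arms, and the graded comparison depends on those arms.

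If the adaptive route were taken, three things would follow:

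- Arm sizes would depart from the stated 20.
- Comparisons with the thinned arms would lose precision.
- Allocation probability would change over calendar time, so a trend over enrolment could bias arm comparisons unless the analysis adjusts for it.

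**Working it through.** **1. The plan's own figure.** 80 participants / 4 arms = 20 per arm. This agrees with the listed sizes, 20 + 20 + 20 + 20 = 80, so the fixed design is internally consistent on size. (The article gives differing arm temperatures in different sections. That is a separate matter and does not affect this point.)

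**2. The passages side by side.**

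| Section | Allocation | Condition |
|---|---|---|
| Statistical Analyses | moves toward better-performing arms at each interim | only where feasible |
| Assignment of Interventions | 1:1:1:1 | none |
| Sample Size Calculation | 1:1:1:1, 20 in each arm | none |

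The two unconditional sections mention no equal run-in phase, no expected rather than final arm size, and no later change of ratio. If adaptation proves feasible, those two sections are wrong. If it does not, the rationale in Statistical Analyses does no work.

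**3. Would an adaptive rule still end near 20 per arm?** The article gives no rule, so this simulation is illustrative and every setting is an assumption:

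- 10 per arm allocated equally, then two blocks of 20;
- each block allocated in proportion to the square root of the posterior probability of being the best arm;
- SD 1, outcomes available at each interim, 4,000 runs per scenario.

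Results:

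- No true difference between arms: single arms range from about 11 to 31 (5th to 95th percentile). Exactly 20/20/20/20 occurs in about 0.05% of runs.
- True means 0, 0.3, 0.6, 0.9 SD with rising temperature, lower taken as better: mean arm sizes about 31/21/16/12.
- Same means, higher taken as better: about 12/16/21/31.

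The arm that gains participants reverses with the undefined meaning of better.

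**4. Cost to one pairwise comparison.** Inputs: the 20 per arm is the article's. The 1.05 SD effect, the two-sided alpha of 0.05 and the unequal splits are assumptions, since the article gives no alpha, SD or standardised effect.

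The variance of a difference in means is proportional to V = 1/n1 + 1/n2. Power comes from the noncentral t distribution with noncentrality 1.05/√V and n1 + n2 − 2 degrees of freedom.

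| Split | V | Change in variance | Noncentrality | Power |
|---|---|---|---|---|
| 20/20 | 0.100 | reference | 3.32 | 90% |
| 25/15 | 0.107 | +7% | 3.21 | 88% |
| 30/10 | 0.133 | +33% | 2.88 | 80% |
| 20/10 | 0.150 | +50% | 2.71 | 74% |

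Mild imbalance costs about 2 points. Only strong imbalance costs 10 points or more.

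**The case against.** The best defence is that the adaptive sentence is conditional. It applies only where feasible, and the same section goes on to refer to standard RCT analyses. On that reading the plan is adaptive if possible and otherwise fixed, and an adaptive rule may be set out in the cited reference or in a fuller document not shown. The hedge is real, and it would be wrong to say that the article commits to response-adaptive allocation. It does not settle the matter, because the two sections that fix the ratio and arm sizes carry no such condition. A later document could supply a rule but could not satisfy both statements as written.

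Several stronger readings are tempting and do not stand:

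- **That no arm can be better in this trial.** A direction could be chosen, such as less weight gain. The article has not chosen one.
- **That favouring the largest HSP response would steer people to the most proinflammatory arm.** The article describes intracellular HSP-70 as anti-inflammatory. It ties the proinflammatory reading to the extracellular-to-intracellular ratio, and its cited cell values for that ratio do not rise steadily with temperature (1.45 at 39 °C, 0.65 at 42 °C, 0.48 at 43 °C, 1.97 at 45 °C).
- **That most participants would be randomised before any interim could help.** No accrual rate is given, there is a 6-week measurement, and the laboratory stay and calorimeter make staggered entry plausible.
- **That adaptation would invalidate a power claim for 20 per arm.** The article makes none. Its power figures are 9 participants (80%) and 75 participants (90%), tied to ranges of the HSP-70 ratio.

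It is also fair to say that specifying an adaptive design in full would remove the conflict equally well, and that calendar-time bias depends on an analysis model not shown.

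**Conclusion.** The point holds in this form: a conditional, allocation-based rationale for Bayesian adaptive methods stands beside an unconditional 1:1:1:1 randomisation of 20 per arm, the two describe different designs, and better-performing is undefined. This rests on the text alone and needs no numerical assumption.

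The size of the consequence does rest on assumptions. With a 1.05 SD effect and two-sided alpha 0.05, pairwise power goes from 90% at 20/20 to between 88% (25/15) and 74% (20/10). The loss is therefore negligible to substantial depending on a rule the article does not state, and these figures illustrate the cost rather than forecast it. The inconsistency still needs resolving before a randomisation list is built, because the ratio determines that list and the arm sizes. The trial has not been initiated, so there is time to do so.

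**What to change.** In Statistical Analyses, remove the rationale about allocating participants to better-performing arms. Keep the fixed 1:1:1:1 randomisation with 20 per arm, as Assignment of Interventions and Sample Size Calculation already state. If Bayesian methods are wanted, say that they will be used to analyse the fixed design without changing the allocation ratio. This suits the stated aim of comparing graded temperatures to study a mechanism.

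The cost is about one sentence. The small downside is giving up an adaptive option for which the article states no driving outcome, direction or interim time.

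If the sponsor prefers to keep that option, the consistent alternative takes more work. It must specify the outcome, the direction, the interim times, the equal run-in, the allocation rule, its operating characteristics and the adjustment for calendar time, and it must restate 20 per arm as a starting or expected size in both other sections.
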